### Data management and statistical analysis

Participants’ entries in electronic diaries and questionnaires will be directly stored in the REDCap software. The research staff will enter manually the rest of the data collected during the screening, the intervention and paper diaries in REDCap. All data will be hosted on a high security server of the Lausanne University Hospital performing automatic continuous backups. All primary outcome data and a random 5% of the rest of the data will be double-checked. Independent and blind coders will inspect diary entries to detect any non-compliance with instructions and count the number of CB-IM. A blind statistician will perform the analyses. To ensure blinding of the coders and the statisticians, they will receive a dataset not indicating which allocation group corresponds to the IIG or WCG. Only the study team will have access to the full coded trial dataset.

For primary outcomes, group differences regarding change of the number of CB-IM between baseline and the 2 weeks postimmediate intervention will be analysed using repeated-measures analyses (intention-to-treat analyses). For the secondary outcomes, repeated-measures analyses will be performed to analyse group differences concerning CB-PTSS between baseline and at 2 weeks postimmediate intervention. Logistic regression analyses will also compare the proportion of participants meeting the diagnostic criteria for CB-PTSD across time and groups. Furthermore, repeated measures analyses will serve to analyse change in the number of CB-IM and CB-PTSS between baseline and follow-up in the IIG. Group differences regarding the proportion of participants meeting the diagnostic criteria for CB-PTSD will be analysed with logistic regression analyses. The mean score of the intervention acceptability will be calculated across both groups. Additional post-hoc analyses conducted will be described as such in publications. Missing data will be dealt with using multiple imputation procedures, if appropriate.

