#### T2: immediate intervention

The IIG will receive the intervention on day 15. For a description of intervention procedures, see the Intervention section.

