#### T3: postimmediate intervention

Both groups will report their CB-IM during the 2 weeks postimmediate intervention. To ensure blinding of WCG, this group will complete a diary covering T1 and T3. Both groups will report their CB-PTSS in a self-report questionnaire during week 2 postimmediate intervention.

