#### T5: postdelayed intervention

The WCG will report their CB-IM in a diary during the 2 weeks postdelayed intervention and their CB-PTSS in a self-report questionnaire during week 2 postdelayed intervention.

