#### T6: follow-up

The IIG will report their CB-IM in a diary during weeks 5 and 6 postimmediate intervention. They will also complete self-report questionnaire assessing postnatal depression and anxiety symptoms, as well as CB-PTSS during week 6 postimmediate intervention. The WCG will not complete follow-up assessments to ensure a fair distribution of burden between groups

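### Withholding the meaning of the group code cannot keep coders and statistician blind once data that only one arm provides are released

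*Protocol article*

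**What the plan says.** The Data management and statistical analysis section gives the coders two tasks: "Independent and blind coders will inspect diary entries to detect any non-compliance with instructions and count the number of CB-IM". It adds that "A blind statistician will perform the analyses". For both roles it names one safeguard, that "they will receive a dataset not indicating which allocation group corresponds to the IIG or WCG". The same section restricts the complete dataset to the study team.

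The study procedures set out different data for the two arms:

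- T2: "The IIG will receive the intervention on day 15". The WCG has its session at T4, on day 30.
- T3: "To ensure blinding of WCG, this group will complete a diary covering T1 and T3".
- T5: "The WCG will report their CB-IM in a diary during the 2 weeks postdelayed intervention".
- T6: "The IIG will report their CB-IM in a diary during weeks 5 and 6 postimmediate intervention", and "The WCG will not complete follow-up assessments to ensure a fair distribution of burden between groups".

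The statistical section also plans an analysis of change from baseline to follow-up in the IIG alone. The Exploratory outcomes section plans one of change around the delayed session in the WCG alone.

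**The concern.** A hidden label blinds only if the rest of the file looks the same in both arms. Here the arms differ by design in which time points are filled. Someone who holds those fields can tell which code is the IIG without being told.

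The primary outcome is the change in the number of childbirth-related intrusive memories (CB-IM) from baseline to the 2 weeks after the immediate intervention. The coders check diary entries and produce that count. The article acknowledges that the research team is not blind and that the comparator is a waitlist, so blind coding and blind analysis are safeguards of real value. If they fail, entries could be accepted more readily in one arm than in the other, and modelling choices could be made with knowledge of the arm.

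**Working it through.** The article gives no figure to reproduce on this point. The check sets the schedule beside the masking measure.

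**Step 1. What each arm contributes** (Study procedures, Table 1, Table 2):

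| Time point | IIG | WCG | Shows the arm? |
|---|---|---|---|
| T1 | Diary, CBTS, EPDS, HADS-A | Same | No, diary layout aside |
| T2, day 15 | Heart rate variability, distress | Nothing | Yes |
| T3 | Diary, CBTS | Diary, CBTS | No, diary layout aside |
| T4, day 30 | Nothing | Heart rate variability, distress | Yes |
| T5 | Nothing | Diary, CBTS | Yes |
| T6 | Diary, CBTS, EPDS, HADS-A | Nothing | Yes |
| T7 | Feedback call | Feedback call | No |

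Any record with T2 or T6 data is IIG. Any record with T4 or T5 data is WCG. Only T1, T3 and T7 are common to both.

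Table 2 adds a trap within T3. The sleep questionnaire and the context-similarity questions are listed at T3/T5. Both refer to the intervention, so they must fall at T3 in the IIG and at T5 in the WCG. A file restricted to T1 and T3 would still show the arm if it kept these items.

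**Step 2. From one woman to the whole arm.** The stated measure implies a group code whose meaning is withheld. If the code stays in the file, one recognised record reveals the meaning for every woman who carries it.

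**Step 3. What the planned analyses require.** The IIG-only follow-up analysis cannot be run without picking out the arm that has T6 data. The WCG-only analysis likewise needs the arm with T5 data. A statistician who runs either knows the codes from then on. The article states no lock of the primary analysis before that.

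**Step 4. What does not require it.** The primary comparison, the group comparison of CBTS scores, and the comparison between groups of the proportion meeting diagnostic criteria over the same interval all rest on T1 and T3. They can be completed before any arm-specific field is released.

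**Step 5. The coders.** Three statements bear on them.

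- The single T1 and T3 diary is presented as something the WCG does. Separate diaries in the IIG are therefore implied, though not stated.
- Table 2 has compliance rated at the end of each diary. A combined diary would give one rating where two separate diaries give two.
- T5 and T6 diaries each belong to one arm. They reveal the arm of the T1 and T3 entries only if coders can link them to the same woman.

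Whether any of this reaches the coders depends on the form of the extract, which the article does not describe.

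**The case against.** The strongest reply is that the article does not say that coders handle the diaries as completed. Electronic entries go straight into REDCap and paper ones are typed in. Coders and statistician then receive a dataset, and the complete dataset stays with the study team. Neither coding task needs physiological data or depression and anxiety scores. The contents of extracts and the order of release are often left to a fuller protocol or a data management plan. Participant blinding, not blind coding, is the article's stated answer to waitlist bias in self-report, and the women log each memory themselves under a written definition.

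Much of this stands. A reader might infer that coders can tell every woman's arm immediately from diary layout alone. The document does not support that: separate IIG diaries are only implied, and what coders receive is not described. A woman who leaves early may also have no arm-specific record at all. Nor does the document show how much discretion coders have over the count.

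Two things do not fall to the reply. The article says that this one measure ensures blinding, and for a statistician who goes on to the single-arm analyses it cannot. Restricting the complete file to the study team does not change that, because those analyses need the arm-specific data.

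There is also a fair objection to an over-strict remedy. Removing all dates and shuffling single entries across women would hinder the coders' check for non-compliance, which may need a woman's entries read together and in time order.

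**Conclusion.** The concern holds in a limited form. The stated measure does not deliver the claimed blinding once T2, T4, T5 or T6 data are supplied, and the article reports no lock of the between-group analyses before that point. This is firm for the statistician. For the coders it is plausible and conditional on the extract they receive.

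A reader might also infer a bias of a definite size, for instance by supposing that coders reject 5 to 10% more post-intervention entries in one arm and concluding that the count shifts by 5 to 10%. That only returns the assumption, since the document gives no rejection rate. The size of any bias cannot be derived, and no figure stated in the article is invalidated.

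Nor does it follow that the primary analysis cannot be blind. It uses only T1 and T3, and an ordered release of data would protect it. The conclusion assumes that the article describes the masking in full. If a fuller document already provides for a restricted extract and a staged release, the article's sentence needs only to say so.

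**What to change.** For the coders: supply only T1 and T3 entries, in one common format for both arms, with no group code, no diary-level layout or compliance fields that differ by arm, and no linked T5 or T6 diaries. Keep the order and times of entries within each woman where the non-compliance check needs them. Code T5 and T6 diaries later, as a separate batch. Free text that mentions the session may still reveal an arm, and this should be acknowledged as a residual limit.

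For the statistician: supply a T1/T3-only file with a dummy arm code, leaving out the sleep and context-similarity items. The exclusion for concurrent psychological treatment, asked at T7 in both arms, can be passed on as a yes/no flag. Release T2, T4, T5 and T6 fields, and the T3 items left out, only after CB-IM coding and the between-group T1 to T3 analyses are locked.

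In the text: replace the statement that blinding is ensured with this sequence, and describe the later IIG-only and WCG-only analyses as unblinded.

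The cost is one export script and a two-step release by whoever manages the data. It needs no extra visits or staff.

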### Developing an evidence-based single-session BI-VT adapted to the perinatal context

A single-session BI-VT was recently adapted to the perinatal context in a pre–post pilot study (n = 18).^27^ During the intervention, participants briefly narrated their childbirth on the maternity ward where they had given birth, as evidence suggests that being in a similar physical context as the one in which the traumatic event occurred improves the chances of successful memory reactivation.^28^ Narration of their childbirth, ensuring a reliable source of the original memory,^29^ lasted 10 min for a sufficient exposure to the reminder cues supposed to engage memory reconsolidation of strong and old memories,^30^ such as trauma-related memories. Participants then played Tetris during 20 min in a neutral room. This single-session BI-VT led to a median reduction of 82% of the number of childbirth-related (CB-)IM.^27^ Participants also reported an average reduction of 57% of CB-PTSS severity at 1 month postintervention and rated the intervention as highly acceptable. Characteristics (distress, nowness and sensorial modalities) of CB-IM were also described in this study, but a larger sample size is needed to better understand the nature of CB-IM and their responsiveness to such intervention.

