### Population, recruitment, group allocation and blinding

Mothers with a minimum age of 18 years, who gave birth at least 6 weeks prior to the screening in one of the two study centres (one university hospital, being the main study centre, and one regional hospital from Switzerland), and suffer from CB-IM will be eligible to participate. To avoid a floor effect regarding CB-IM reduction, we will only include mothers reporting at least four CB-IM over the 2 weeks prior to the screening. Exclusion criteria will be insufficient French-speaking level to complete the assessments, established intellectual disability or psychotic illness, an ongoing psychological treatment in relation to childbirth, propranolol medication (due to suspected effects on memory reconsolidation^39^), alcohol and/or illicit drug abuse, being pregnant, perinatal loss of a child born during the index traumatic childbirth (ie, the childbirth triggering the CB-IM targeted during the intervention) or a life-threatening illness of the mother or infant(s). Moreover, mothers not able to distinguish potential IM related to another traumatic event from CB-IM linked to the index traumatic childbirth will be excluded. Importantly, data related to any participants that reported less than two CB-IM at baseline will be excluded from relevant analyses to avoid a floor effect, or if they stated having a concurrent psychological treatment in relation to childbirth during study participation.

Adverts will be displayed in nurseries and practices of midwives, gynaecologists and paediatricians. Study information will also be shared on social media. In addition, study centres will send a text message to invite potentially eligible mothers who gave birth in their hospitals to participate in the study.

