During a phone call, the study coordinator (DF) will screen interested mothers. The presence and number of CB-IM over the past 2 weeks will be assessed with the item B1 of the Clinician-administered PTSD scale for Diagnostic and Statistical Manual of Mental Disorders, Fifth Edition, (DSM-5),^40^ and the T-ACE will be used to assess alcohol consumption.^41^ Eligible mothers who signed the consent form will be randomly allocated to the IIG or WCG with a 1:1 ratio. To ensure concealment, a scientific collaborator not involved in data collection created a block randomisation list stratified by centre, which will be automatically generated by the Research Electronic Data Capture (REDCap) software. To limit waitlist condition-related bias on participants’ self-reports,^32 33^ participants will be blind to group allocation. To that matter, participants will only be informed that both groups will complete the same assessments and receive the intervention, but in a different order. For an overview of study procedures for both groups, see figure 1. To improve completion of study assessments, the study coordinator will follow participants’ progression during the whole study and participants will receive reminders to complete questionnaires.

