### Primary outcome

The primary outcome will be the difference in the number of CB-IM between baseline and the 2 weeks postimmediate intervention across groups.

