### Sample size calculation

A sample size calculation was conducted for our primary and secondary outcomes based on the results obtained from the pilot study,^27^ assessing the efficacy of the same intervention using a single-group pre–post design, and from laboratory studies using RCT designs to assess the efficacy of a similar BI-VT.^23 24^ A sample size of 90 participants (45 allocated in each group) is estimated to be necessary to detect the effect of the intervention on our primary and secondary outcomes with an 80% power (α = 0.05). Based on our experience with this study population,^11 27^ a conservative estimate of a 30% drop-out and exclusion was assumed. We therefore plan to recruit 120 participants in total.

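### Read in the ordinary way, the primary repeated-measures test of change in CB-IM counts does not condition on baseline; it is valid but gives away power that baseline adjustment would recover

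*Protocol article*

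**What the plan says.** The Primary outcome section states: "The primary outcome will be the difference in the number of CB-IM between baseline and the 2 weeks postimmediate intervention across groups". The section on data management and statistical analysis gives the method: "group differences regarding change of the number of CB-IM between baseline and the 2 weeks postimmediate intervention will be analysed using repeated-measures analyses". Table 1 of the article shows that both arms keep diaries at T1 (baseline) and T3 (the two weeks after the immediate intervention), so the primary contrast rests on two time points.

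Three other statements bear on the choice of analysis:

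- **Entry and analysis thresholds.** In the section on population and allocation, "we will only include mothers reporting at least four CB-IM over the 2 weeks prior to the screening", and "data related to any participants that reported less than two CB-IM at baseline will be excluded from relevant analyses". No upper limit is given.
- **Earlier evidence.** The intervention in the pilot (single group, n = 18) "led to a median reduction of 82% of the number of childbirth-related (CB-)IM".
- **Randomisation.** A collaborator not involved in data collection "created a block randomisation list stratified by centre".

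The article names no distribution, link, transformation or covariate for the primary model.

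**The concern.** With two time points, the group-by-time interaction in an ordinary repeated-measures analysis is algebraically the between-arm t test on change (T3 minus T1). A change score subtracts the whole baseline count, as if it predicted the follow-up count with a slope of 1. Women enter on a two-week count, which is a noisy measure, so the true slope will usually be below 1. The subtraction then adds noise that conditioning on baseline would remove.

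A second issue is scale. If a few women have very high counts and the intervention lowers counts by a proportion, those women dominate the variance of an absolute difference.

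What is at stake is power: the trial could miss a moderate real effect although it already collects the baseline count that would sharpen the test. Validity is not at stake.

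**Working it through.** **The plan's own figure.** The Sample size calculation section gives 90 participants (45 per arm) for 80% power at α = 0.05. It states no effect size, SD or correlation, so 90 cannot be rebuilt from inputs. Solving backwards (two-sided, normal approximation), the detectable standardised difference is (1.960 + 0.842) × √(2/45) = 0.59. This serves only as the reference point: assume that the change-score test has exactly 80% power at 45 per arm.

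**Step 1: baseline adjustment, no skewness assumed.** Let r be the within-arm correlation between T1 and T3, with equal variance σ² at both.

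- Variance of change: 2σ²(1 − r)
- Residual variance after conditioning on baseline: σ²(1 − r²)
- Ratio: (1 − r²) / [2(1 − r)] = (1 + r)/2
- Power after adjustment: Φ(2.802/√ratio − 1.960)
- Number per arm for 80% power: 45 × ratio, rounded up

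| r (assumed) | Variance ratio | Power at 45 per arm | Per arm for 80% |
|---|---|---|---|
| 0.3 | 0.65 | 93.5% | 30 |
| 0.5 | 0.75 | 89.9% | 34 |
| 0.7 | 0.85 | 86.0% | 39 |
| 0.9 | 0.95 | 82.0% | 43 |

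Equal variances are not needed for the direction of the result. If the T3 SD is k times the T1 SD, the change-score variance exceeds the adjusted variance by σ²(1 + k² − 2rk) − σ²k²(1 − r²) = σ²(1 − rk)², which is never negative.

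**Step 2: skewed counts with a proportional effect.** The article gives no mean, SD or skewness, so every input here is an assumption: individual rates lognormal with mean 12 per two weeks; Poisson counts with gamma visit noise; screening count at least 4 and baseline at least 2 (these two from the article); 45 per arm; 1,000 replicates. The resulting baseline skewness was about 1.8 to 3.2 and the T1–T3 correlation 0.29 to 0.66. Columns give the T3 rate relative to baseline, intervention v control. Cells give power (%) for raw change / ANCOVA on raw counts / ANCOVA on log(count+1).

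| Log-SD, noise shape | 0.5 v 1.0 | 0.6 v 1.0 | 0.5 v 0.8 | 0.4 v 0.8 | 0.18 v 0.8 |
|---|---|---|---|---|---|
| 0.5, 5 | 90/99/100 | 70/93/93 | 55/87/84 | 75/99/100 | 98/100/100 |
| 0.8, 5 | 83/98/99 | 67/85/89 | 44/75/80 | 66/96/99 | 94/100/100 |
| 1.0, 5 | 76/95/99 | 58/77/89 | 38/67/79 | 58/93/98 | 84/100/100 |
| 0.8, 2 | 54/84/88 | 35/58/63 | 24/48/54 | 40/81/87 | 75/100/100 |

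- In the first four effect columns, raw change loses about 10 to 40 points against log ANCOVA in most cells; the largest loss is 47 (39.6% v 87.0%).
- In the last column, where the intervention arm falls by the pilot's 82%, the loss is 2 to 25 points and raw change still has 75–98% power.
- Conditioning on baseline without any transformation recovers most of the loss. With log-SD 0.8, shape 5 and 0.5 v 0.8, power rises from 44% to 75%, against 80% for log ANCOVA. That is 31 of 36 points.

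**Step 3: type I error.** Under no group difference (log-SD 0.8), raw change rejects in 4.3–5.0% of replicates and log ANCOVA in 4.0–5.0%. A Poisson model with robust errors rejects in 5.8–8.1%. A negative binomial Wald test, in a separate set of assumed scenarios with 400 replicates, rejects in 4.8–8.7%.

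**The case against.** The strongest reply is that the article does not state the model criticised here. A repeated-measures analysis can be a Poisson or negative binomial mixed model, whose group-by-time term is a ratio. It can also be a model with a common baseline mean, which is about as efficient as ANCOVA. A reader might infer that the plan commits to an untransformed Gaussian model of absolute change; the text excludes none of the alternatives. This stands, and it is why the point is conditional on the ordinary reading. The wording of the outcome as a difference in number does lean that way.

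A reader might also infer that centre is left out of the analysis. The article lists no covariates at all, and a condensed article commonly leaves them to the full protocol or SAP. That inference is not supported, and the gain from a centre term has not been quantified.

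Skewness and a proportional effect are likewise not established. A median percentage reduction in 18 women is a descriptive summary. The absolute reduction in intrusions is also a legitimate target, and preferring a ratio is partly a matter of judgement.

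These replies do not touch Step 1, which needs neither skewness nor a ratio scale and applies whenever the test is run as a change-score comparison.

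**Conclusion.** The point holds in a conditional form. Run as an ordinary group-by-time test, the primary analysis is valid but inefficient. Taking 80% power at 45 per arm as the reference, conditioning on baseline raises it to about 86–93% for correlations of 0.7 down to 0.3, and gains little at 0.9 (82%). This rests on an assumed correlation and equal variances.

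The larger losses rest wholly on assumed spread, control-arm course and effect. Some scenarios put raw-change power below 50%, and a reader might infer that the trial is that badly underpowered. The documents do not support such a figure: they give no spread, and with an effect near the pilot's the same test has 75–98% power. The pilot was uncontrolled, however, so a smaller net effect is plausible, and that is where efficiency matters. The change is worth making because it costs almost nothing, not because the present analysis is wrong.

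**What to change.** Before unblinding, fix one primary test:

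- **Primary.** ANCOVA of the T3 CB-IM count conditioned on the baseline count, with centre as the stratification factor, preferably with both counts as log(count+1). A repeated-measures model with a common baseline mean and a centre term is an acceptable equivalent. Name one of them as primary.
- **Reported beside it.** The absolute between-arm difference in counts with its 95% CI, so that the outcome as the article words it remains visible.
- **Sensitivity only.** A negative binomial rate ratio with log baseline count and centre, with a permutation or small-sample p-value because the Wald test can be liberal at this size.
- **CBTS.** Analyse T3 CBTS the same way, adjusted for baseline CBTS and centre. Step 1 applies with that scale's own correlation; no separate calculation was made for it.

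The cost is a wording change in the protocol or SAP. Baseline counts and centre are already collected. The real downside is that on the log scale the headline effect is proportional, which changes the estimand from an absolute difference. If the investigators want to keep the absolute scale, ANCOVA on untransformed counts does so and, in the assumed scenarios, still recovers most of the lost power.

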### Secondary outcomes

Secondary outcomes will be:

The change in CB-PTSS between: (a) baseline and at 2 weeks postimmediate intervention across groups, (b) baseline and follow-up in the IIG.The change in the number of CB-IM between baseline and follow-up in the IIG.The acceptability of the intervention in both groups.

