#### City Birth Trauma Scale (CBTS)

This questionnaire assesses CB-PTSS during the past week, and diagnostic criteria of PTSD according to the DSM-5.^44^ Twenty-two items, using a 4-point Likert scale, assess the four CB-PTSS clusters (*re-experiencing*, *avoidance*, *negative cognitions and mood*, *hyperarousal*). Original instructions of the CBTS will be adapted for participants who had multiple childbirth(s) to complete the questionnaire regarding the index traumatic childbirth. Good psychometric properties were found for the French version of the CBTS.^45^

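### CB-PTSD status is to be compared across time and groups by logistic regression with no stated handling of repeated measurements; a baseline-adjusted T3 comparison is safer and more powerful, and a second logistic sentence lacks a time point

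*Protocol article*

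**What the plan says.** All of the analysis wording is in the protocol article under Data management and statistical analysis. For the CB-PTSS score, "repeated-measures analyses will be performed to analyse group differences concerning CB-PTSS between baseline and at 2 weeks postimmediate intervention". For the diagnosis, the next sentence reads "Logistic regression analyses will also compare the proportion of participants meeting the diagnostic criteria for CB-PTSD across time and groups". The text then turns to follow-up: "repeated measures analyses will serve to analyse change in the number of CB-IM and CB-PTSS between baseline and follow-up in the IIG". Directly after that comes "Group differences regarding the proportion of participants meeting the diagnostic criteria for CB-PTSD will be analysed with logistic regression analyses", with no time point.

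The diagnosis comes from the City Birth Trauma Scale (CBTS): "This questionnaire assesses CB-PTSS during the past week, and diagnostic criteria of PTSD according to the DSM-5". Both groups complete it at T1 and again at T3: "Both groups will report their CB-PTSS in a self-report questionnaire during week 2 postimmediate intervention". At T6 only the IIG completes it: "The WCG will not complete follow-up assessments to ensure a fair distribution of burden between groups". The Secondary outcomes section sets the CB-PTSS comparisons accordingly: "a) baseline and at 2 weeks postimmediate intervention across groups, (b) baseline and follow-up in the IIG".

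**The concern.** Two things in this paragraph need settling.

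First, a comparison of proportions over time and between groups uses two binary records per woman. The paragraph allows for that dependence when it deals with the score but names only logistic regression for the status derived from the same questionnaire. A reader who follows the words literally could stack the T1 and T3 records and fit an ordinary logistic model. The standard errors would then be wrong, in a direction that depends on which coefficient is reported, and the text does not say which coefficient is the test. A group-by-time contrast is also a weak way to use a baseline measurement in a randomised trial, even when the correlation is handled properly.

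Second, the last logistic sentence can be read with the follow-up sentence before it, where no control data exist, or as a repeat of the T3 comparison. Either way it is unclear how many between-group tests of CB-PTSD status are planned, and at which time.

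**Working it through.** **Is there a figure to reproduce?** No. The Sample size calculation section gives 90 evaluable women (45 per group), 80% power and α = 0.05, but no assumption about the CB-PTSD proportion. Only the 45 per group is used below. The prevalence p and the within-woman correlation ρ are assumptions, because the article gives neither.

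**Standard errors if T1 and T3 records were stacked as independent.** Take a logistic model with group, time and their interaction, and a common prevalence p. The variance of each cell's logit is v = 1/(n·p·(1 − p)). With n = 45 and p = 0.35, v = 1/10.24 = 0.0977.

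- Group-by-time interaction: ordinary SE = √(4v) = 0.625; correct SE = √(4v(1 − ρ)). The ratio is 1/√(1 − ρ), whatever p is.
- Time-averaged group effect: ordinary SE = √v = 0.313; correct SE = √(v(1 + ρ)). The ratio is 1/√(1 + ρ).
- Actual type I error at nominal 5% = 2(1 − Φ(1.96 × ratio)).

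| ρ (assumed) | Interaction: correct SE | Ratio, ordinary/correct | Actual type I error | Time-averaged effect: ratio | Actual type I error |
|---|---|---|---|---|---|
| 0.3 | 0.523 | 1.20 | 1.9% | 0.88 | 8.6% |
| 0.5 | 0.442 | 1.41 | 0.6% | 0.82 | 11.0% |
| 0.7 | 0.342 | 1.83 | 0.03% | 0.77 | 13.3% |

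A null simulation (1,500 runs per correlation, 45 per arm, p = 0.35) agrees. At ρ = 0.3, 0.5 and 0.7 the ordinary model rejected in 2.7%, 0.3% and 0.0% of runs for the interaction, and in 9.0%, 10.9% and 14.2% for the time-averaged effect. Variance clustered on woman brought these to 4.6-5.6% and 4.3-5.7%.

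**Power of the possible analyses.** Assumed rates: 40% at T1 in both arms; at T3, 35% in the WCG and 12% in the IIG; 45 per arm; moderate and then stronger within-woman correlation. With 40% at T1 and 35% at T3 in both arms, the ordinary interaction SE is √(2/(45 × 0.40 × 0.60) + 2/(45 × 0.35 × 0.65)) = √(0.185 + 0.195) = 0.62. The simulated spread of the estimate under the null was 0.51 and 0.45, so the ordinary SE is 0.62/0.51 = 1.22 and 0.62/0.45 = 1.38 times too large.

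| Analysis | Simulated power |
|---|---|
| Interaction, ordinary logistic | 50-52% |
| Interaction, variance clustered on woman | 62-71% |
| T3 status on arm, adjusted for baseline status | 77-80% |

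A separate run (500 replicates, random-intercept logistic model with SD 1.5 and 2.5) gave 51-53%, 63-74% (by GEE) and 78-82%. The ordering is stable.

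**The second logistic sentence.** The paragraph runs in two pairs: score to T3 between groups, then status; score to follow-up in the IIG, then status again. Read in that order, the last sentence belongs to follow-up. The T6 section, Table 1 (CBTS at T6 for the IIG only) and the Secondary outcomes section all exclude a group comparison there. Read instead as T3, it repeats the earlier logistic sentence.

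**The case against.** The strongest reply is that the article nowhere says the regression is ordinary or assumes independent records. Mixed-effects logistic regression and logistic GEE are both logistic regression, and separate regressions at each time point would use one record per woman. Every analysis in the paragraph is described only by method family, the primary one included, and an article commonly leaves model form to the full protocol or SAP. This stands. A reader might infer that the plan will produce wrong standard errors; the document does not support that, and the first table shows only what would follow from one possible implementation.

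A reader might also infer that the plan commits itself to an impossible group comparison at T6. It does not: the sentence names no time point, and the rest of the article confines group comparisons of CB-PTSS to T3. The defect is ambiguity or duplication.

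The step from 62-71% to 77-80% is not the repair of a standard error. It comes from choosing a better contrast and using baseline as a covariate, and the adjusted odds ratio is a somewhat different quantity from the interaction. That is fair, but under randomisation both address whether the intervention changes diagnosis at T3, and the better contrast costs nothing.

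Finally, the CB-PTSD proportion is not itself listed among the primary, secondary or exploratory outcomes; it supports the secondary CB-PTSS score. This limits the stakes. What survives is that the comparison across time and groups is written into the plan, is open to an invalid implementation, and is less efficient than an available alternative even when implemented correctly.

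**Conclusion.** The point holds in a conditional form. The plan compares repeated CB-PTSD status across time and groups without naming a method for within-woman correlation, in contrast to its treatment of the scores. If the records were stacked as independent, the group-by-time standard error would be about 20% to 40% too large at correlations of 0.3 to 0.5, making the test conservative. A time-averaged group effect would err the other way, with type I error of about 9% to 11% over the same range.

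The firmer part does not depend on how the unseen analysis plan handles the correlation: a correct time-by-group test has about 62-71% power where baseline-adjusted T3 status has about 77-80%. Those figures rest on assumed rates (40% at T1; 35% v 12% at T3), assumed moderate to strong correlation and 45 evaluable women per arm. Other rates would change the levels. The second logistic sentence needs a time point; only T3 is possible for a group comparison. The matter is worth correcting but does not touch the primary outcome.

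**What to change.** - Make the between-group CB-PTSD analysis a logistic regression of T3 status on arm, adjusted for baseline CB-PTSD status (or baseline CBTS score) and for centre, the stratification factor.
- If a time-by-group model is kept, state that it is a GEE or mixed logistic regression clustered on woman, and that the group-by-time term is the test.
- Tie the second logistic sentence to T3, or delete it as a duplicate.
- Report CB-PTSD status at T6 as a within-IIG result only, because the WCG has no T6 assessment.

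The cost is two sentences of analysis wording. Baseline status, CBTS score and centre are already collected, so no new data, visits or participants are needed.
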